### Procedure

Based on the predetermined randomization envelopes, participants will be randomly allocated to the intervention group or control group (Figure 1). The patients will have an equal probability of being assigned to either of the two groups. Participants will be asked to record symptoms in a rhinitis diary from the run-in period to the 4th week after randomization, and the usage of acute symptomatic relief medication will be recorded during the treatment period. The case report form contains all of the outcome measures and the rhinitis diary will be collected separately from the four hospitals in the 4th week after randomization by blinded interviewers. Blinded telephone interviewers will contact the participants regarding the days of moderate to severe allergic rhinitis during the 4 weeks after the treatment period to evaluate the long-term effect of acupuncture in the 8th week after randomization.

**Figure 1 Fig1:**
[figure not shown]
CONSORT flow diagram.

### Interventions

Participants will undergo a standardized interview and receive further information regarding the study. Acupuncturists for the control group must have over 10 years of clinical experience and an acupuncture license issued by the Ministry of Health of the People’s Republic of China. In addition to these criteria, acupuncturists for the interventional group must have been trained by [name], the inventor of the sphenopalatine ganglion stimulation technique; have relevant neuroanatomic knowledge; be able to perform the technique clinically; have practiced no fewer than 10 times under [name] supervision; and have practiced independently no fewer than 2,000 times. Before the trial, all acupuncturists will receive special training in the purpose and procedures of the trial, therapeutic strategies, and quality control.

Patients will receive 4 weeks of treatment. In the interventional group, the acupuncturists will use one disposable sterile acupuncture needle (0.35 mm diameter, 60 mm length; Beijing Zhongyan Taihe Medicine Co., Beijing, China) to stimulate the sphenopalatine ganglion. After local disinfection, the needle will be gradually inserted between the zygomatic arch and the coronoid process of the mandible to a depth of approximately 55 mm to enter the pterygopalatine fossa. An additional picture file shows this in more detail [see Additional file 1]. Once the needle touches the sphenopalatine ganglion and the patient experiences a special sensation (radiating toward the nose), the patient will signal with the hand and the needle will be withdrawn immediately. The sphenopalatine ganglion will be stimulated unilaterally in a session. Patients will receive 1 or 2 sessions a week, but most will need only 1 weekly session. The physician will decide whether another session is required on the basis of physical signs and symptoms during the second visit of the week.

The control group will undergo 2 sessions of verum acupuncture per week. The acupoints, including the main and adjunct points (Table 1), have been selected on the basis of Chinese medicine guidelines for allergic rhinitis [14] and are described according to standard nomenclature [15]. Two main and two adjunct points will be applied according to each patient’s symptoms. In particular, 32-gauge (0.25 mm diameter, 25 mm length) sterile needles (Beijing Zhongyan Taihe Medicine Co.) will be used for facial, head, and back points, whereas 30-gauge (0.3 mm diameter, 40 mm length) sterile needles (Beijing Zhongyan Taihe Medicine Co.) will be used for limb and lumbar points. The depth of insertion will vary between 10 and 30 mm (details in Table 1). The acupuncturists will manually manipulate the acupuncture needles until *de-qi* (that is, sensation of tenseness around the needle felt by the practitioner and numbness, distension, soreness, and heaviness around the acupoint felt by the patient) and maintain the needle position for 25 minutes.

**Table 1 Tab1:** **Verum acupuncture points and techniques for moderate-severe persistent allergic rhinitis**

**Acupoint**	**Direction**	**Depth (mm)**
Main		
Yingxiang (LI20), both	Transversely along the nasolabial sulcus and toward the root of the nose	10 to 15
Yintang (GV29)	Transversely and downward toward the nose	10 to 15
Fengchi (GB20)	Obliquely toward the tip of the nose	13 to 20
Fengfu (GB16)	Perpendicular to the skin	13 to 20
Zusanli (ST36)	Perpendicular to the skin between the tibia and the fibula	20 to 30
Adjunct		
Shangxing (GV23)	Transversely toward the calvarium	8 to 13
Hegu (LI4)	Perpendicular to the skin	13 to 25
Kouheliao (LI19)	Obliquely toward the tip of the nose	5 to 8
Feishu (BL13)	Obliquely toward the spine	13 to 20
Pishu (BL20)	Obliquely toward the spine	13 to 20
Shenshu (BL23)	Perpendicular to the skin	15 to 25
Sanyinjiao (SP36)	Perpendicular to the skin	13 to 25

### Outcome measures

The primary outcome measure is the change in TNSS between the baseline (week 0) and week 4. The secondary outcome measure include the change in TNNSS between the basline (week 0) and week 4, onset time and duration of effectiveness in every session, change in the number of symptomatic days from the baseline to the end of the follow-up (week 8), change in total IgE level and eosinophil count in venous blood from the baseline to week 4, change in RQLQ score from the baseline to week 4, and clinical waiting time (Table 2).

**Table 2 Tab2:** **Outcome measurements**

**Week**	**0**	**1**	**2**	**3**	**4**	**5**	**6**	**7**	**8**
	**Baseline**	**Treatment period (4 to 8 session)**							**Follow-up**
Sign informed consent	√								
TNSS	√	√	√	√	√				
TNNSS	√	√	√	√	√				
Physical sign	√	√	√	√	√				
RQLQ score	√	√	√	√	√				
IgE level	√				√				
Eosinophil count	√				√				
Number of days with moderate-severe PER in the last month	√								√
Allergen test	√								
Randomization	√								
Onset time		√	√	√	√				
Duration of effectiveness in every session		√	√	√	√				
Waiting time		√	√	√	√				
Adverse event		√	√	√	√				

TNSS, Total nasal symptom score; TNNSS, Total non-nasal symptom score; RQLQ, Rhinoconjunctivitis Quality of Life Questionnaire.

Onset time is the timing of changes in the physical sign score and nasal congestion degree. The physical sign score will be calculated from the degree of inferior nasal concha swelling [16] before and after each session. The nasal congestion degree will be scored using a visual analog scale [17] before and after each session. The duration of effectiveness will be recorded as the duration of change in TNSS after each session (once the patient feels symptom alleviation).

### Data collection

During the study, data will be collected before and after each session and in weeks 0, 4 and 8. The physical sign score will be calculated by outcome assessors approximately 10 to 18 times (week 0, before and after each session), and the RQLQ score will be subjectively determined at least five times (once a week). The total IgE level and eosinophil count in venous blood will be measured in weeks 0 and 4.

Participants will be asked to record symptoms from the baseline to week 4 in a rhinitis diary. They will be required to note the use of relief medication (cetirizine dihydrochloride film-coated tablets) prescribed by the physicians for acute symptoms of allergic rhinitis, including dosage, ingestion time, relief time, and side effects. The case report form containing data for outcome measures and the rhinitis diary will be collected separately from the hospitals by blinded interviewers in week 4. Blinded telephonic interviewers will contact participants regarding the number of moderate-severe symptomatic days with PER up to week 8. Participants will also be asked to report any adverse events including discomfort, bruising, or subcutaneous hematoma around the insertion site; nausea; or feeling faint after each treatment.

Compliance and reasons for discontinuation will be documented in the case report form until week 8. In dropout cases, participants will be contacted by telephone or mail to ascertain the reasons and record the time of the last treatment and last assessment. For withdrawal caused by adverse events or dissatisfaction with the treatment, participants will receive other suitable treatments.

### Statistical analysis

Data will be analyzed by the following principles: (i) intention-to-treat analysis (participants who have at least one measurable outcome after treatment; missing data will be replaced according to the principle of last observation carried forward) and (ii) and per-protocol analysis (participants who have completed the study). A variance analysis will be performed to reject the global hypothesis that “There is no difference in all fields of means between the groups.” The significance level is 5%; therefore *P* <0.05 indicates a significance difference.

The means of TNSS and TNNSS will be compared by analysis of variance (ANOVA) for repeated measures between the groups. Mean onset time and duration of effectiveness will be compared by *t*-test between the groups. Analysis of variance (ANOVA) for repeated measures will be used for between-group comparisons of RQLQ scores. The other continuous variables (total IgE level and eosinophil count in venous blood, number of symptomatic days, and clinical waiting time) will be compared by *t*-test. Comparisons within groups will be performed by multivariate ANOVA followed by Tukey’s post hoc test. Stratified analysis within the four hospitals will be performed to control for confounding factors, if necessary. The incidence of adverse events will be calculated and compared between the groups by using the chi-squared test or Fisher’s exact test. All analyses will be performed in SPSS version 13.0 (SPSS, Chicago, IL).

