### Sample size

We used the symptomatic outcome of the pilot study (10:10 cases in each group) to calculate the sample size in PASS 2008 software (NCSS, Kaysville, UT). The means for the score of TNSS, serially assessed during the 4-week treatment period, was 4.2071 ± 2.58702 after sphenopalatine ganglion stimulation and 7.4393 ± 2.0368 after verum acupuncture. For a power of 0.9 to detect a significant difference (α = 0.01, two sided), 15 participants per group are required. Forty cases will be enrolled in consideration of four centers’ research capabilities. Allowing for a 20% dropout rate, 48 participants will be enrolled in each group, yielding 96 patients for the study.

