Our pilot study revealed that sphenopalatine ganglion stimulation with one acupuncture needle yields significant differences in onset time, duration of effectiveness, TNSS, RQLQ score, and number of post-treatment symptomatic days compared with verum acupuncture. Experts in allergic rhinitis were consulted to decide which endpoints to adopt for sample size calculation. They concluded that changes in TNSS are generally applied, and this scoring system has been validated [18]. Therefore, the mean TNSS was used to calculate the sample size for the trial. Furthermore, the research group consensually decided that TNSS should replace onset time and duration of effectiveness, reported in the ISRCTN registry, as the primary outcome measure of the trial. Only 15 cases per group, total 30, are needed based on the sample calculation. As the small sample size may be increase the risk of bias, we decided to increase the patient number to 40 in each group in consideration of each center’s research capabilities. Allowing a drop-out rate of 20%, 96 participants will be enrolled in the study. All other endpoints are considered as secondary outcome measures. The total IgE level and eosinophil count in venous blood will be measured to investigate the mechanism underlying the effect of acupuncture.

We will measure the clinical waiting time to investigate economic benefits. Sphenopalatine ganglion stimulation with an acupuncture needle requires only approximately 1.5 min and no bed. In contrast, patients spend an average of 2 h to receive acupuncture in Chinese hospitals, including 1.5 h or longer waiting for a bed and 20 min or longer per session.

The proposed trial has several methodological limitations. The acupuncturists and participants cannot be blinded because of the difference in acupuncture techniques and control required while needling. However, the acupuncturists will be trained to not communicate the therapeutic procedures and responses to the participants and outcome assessors. Furthermore, this study will not allow us to determine whether the observed efficacy is caused by placebo effects, intensity of provider contact, or physiological effects of needling. The bias resulting from the lack of blinding cannot be totally excluded. Finally, the sample size is small.

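### The sample size uses two-sided alpha 0.01 and the analysis 5%, the stated 15 per group matches neither, and an undefined global test does not bear on the primary outcome

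*Protocol article*

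**What the plan says.** **Sample size.** The pilot TNSS "was 4.2071 ± 2.58702 after sphenopalatine ganglion stimulation" and "7.4393 ± 2.0368 after verum acupuncture", with ten patients per group. The calculation reads "For a power of 0.9 to detect a significant difference" and continues ("α = 0.01, two sided), 15 participants per group are required". The target is then raised to 40 per group because of the centres' capacity, and to 48 per group for 20% dropout. The Discussion repeats this account.

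**Statistical analysis.** "A variance analysis will be performed to reject the global hypothesis that" the groups show no difference across all fields of means. The fields are not listed. The section goes on: "The significance level is 5" per cent, so that P below 0.05 counts as significant. It then assigns a test to each outcome: repeated-measures ANOVA for TNSS, the non-nasal score (TNNSS) and the quality-of-life score (RQLQ), and t-tests for the other continuous outcomes, including clinical waiting time.

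**Outcome measures and Discussion.** Change in TNSS from week 0 to week 4 is the only primary outcome; all others are secondary. On time, the Discussion says "Sphenopalatine ganglion stimulation with an acupuncture needle requires only approximately 1.5 min and no bed", against an average of 2 hours for conventional acupuncture, of which 1.5 hours or more is waiting for a bed.

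**The concern.** Three things in the stated text do not fit together.

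1. The error rate used to size the trial differs from the one used to judge it, and no reason is given. A reader cannot tell whether 0.01 was a deliberate margin or a slip.
2. The stated 15 per group does not follow from the stated inputs at either alpha.
3. The only null hypothesis written out in the analysis section is a global one over unnamed variables. It is not the hypothesis for the primary outcome.

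What is at stake is how the result is read. A rejected global null could be reported as an overall difference between the techniques when it reflects only how long patients wait for a bed. It could also be taken as licence to read nine separate 5% tests as if multiplicity had been dealt with.

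**Working it through.** **Inputs from the Sample size section.** Means 4.2071 and 7.4393; SDs 2.58702 and 2.0368; power 0.90; equal groups.

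- Difference = 7.4393 − 4.2071 = 3.2322
- SD = √[(2.58702² + 2.0368²)/2] = √[(6.6927 + 4.1486)/2] = 2.328
- Standardised difference = 3.2322/2.328 = 1.388

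**Step 1: reproduce the stated 15.** Normal approximation: n per group = 2(z₁₋α/₂ + z₀.₉₀)²/1.388².

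- Two-sided 0.01: 2 × 3.857²/1.388² = 15.44, so 16
- Two-sided 0.05: 2 × 3.242²/1.388² = 10.90, so 11

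Exact power from the noncentral t distribution with 2n − 2 degrees of freedom:

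| n per group | Power, two-sided 0.01 | Power, two-sided 0.05 |
|---|---|---|
| 11 | 65.9% | 87.2% |
| 12 | 71.4% | 90.1% |
| 15 | 84.1% | 95.6% |
| 17 | 89.6% | 97.5% |
| 18 | 91.7% | 98.1% |

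The exact requirement is 18 at 0.01 and 12 at 0.05. At 15 per group and two-sided 0.01, power is 84% by t and 89% by normal approximation, so short of 90% either way. Fifteen does come out of an exact t-test at one-sided 0.01 (power 90.1%). That may explain the figure, but the document says two-sided.

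**Step 2: does the planned size suffer?** At 40 per group and the pilot difference, exact power is 99.98% at 0.01 and above 99.99% at 0.05. At 38 per group (48 less 20% is 38.4) it is still 99.96% at 0.01. So no.

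**Step 3: what the choice of alpha changes.** The smallest significant difference at 40 per group is t × 2.328 × √(2/40) = t × 0.5206.

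- At 5%: 1.991 × 0.5206 = 1.04 points
- At 1%: 2.640 × 0.5206 = 1.37 points

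This uses a plain two-sample comparison with the pilot SD.

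**Step 4: the global test.** The document gives neither the fields nor an SD for waiting time, so both are assumed here. The fields are taken as the nine continuous outcomes named in the section: TNSS, TNNSS, onset time, duration of effectiveness, RQLQ, total IgE, eosinophil count, symptomatic days and waiting time. They are taken as uncorrelated, with 40 per group and a Hotelling T² test at 5%. Only waiting time differs, by 90 minutes (the Discussion's 1.5 hours). The noncentrality is (40/2) × (90/SD)², referred to F with 9 and 70 degrees of freedom (critical value 2.017).

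| Assumed SD of waiting time (min) | Noncentrality | Chance of rejecting the global null |
|---|---|---|
| 30 | 180 | about 100% |
| 60 | 45 | 99.9% |
| 90 | 20 | 86% |
| 120 | 11.25 | 56% |

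**Step 5: does it protect anything?** In 3,000-run simulations with waiting time shifted by 1.5 SD, no other effect and correlations between outcomes of 0, 0.3 or 0.5:

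- the global test rejected in 99.8% to 100% of runs;
- TNSS was falsely significant in about 4% to 6% of runs, the same whether or not a significant global test was required first;
- at least one of the eight null outcomes (all but waiting time) was significant in about 25% to 33% of runs.

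The independence formula for eight gives 1 − 0.95⁸ = 33.7%. Leaving TNSS out, seven secondary outcomes give 1 − 0.95⁷ = 30.2%.

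**The case against.** The best reply is that the document does contain a usable rule. It names one primary outcome, assigns TNSS a test and sets P below 0.05. The 0.01 belongs to a planning calculation, and sizing at a stricter alpha than the test uses is conservative. The 15 was never used, and 15 against 15.44 is close to a rounding matter by the normal approximation. Handling of multiplicity among secondary outcomes is commonly left to a statistical analysis plan. All of this stands, and it limits the point.

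Stronger readings are tempting, but the text does not support them:

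- **That there is no valid decision rule for TNSS.** There is one, and its type I error stays near 5% (step 5).
- **That a TNSS P value between 0.01 and 0.05 succeeds under one section and fails under the other.** The Sample size section states no success criterion; only the analysis section does.
- **That the global test is a gate, or that waiting time is certain to reject it.** No order or dependence is stated, the fields are unlisted, waiting time also has its own t-test, and no SD is given.
- **That nine tests carry a 37% false-positive risk (1 − 0.95⁹).** That counts waiting time as a true null although the Discussion expects it to differ.

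What the reply does not remove is the unexplained pair of alphas, a sample-size figure that misses its stated power, and a stated hypothesis that is undefined and is not the primary one. These are faults in text that is present, not details left to another document.

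**Conclusion.** The inconsistency is real and should be corrected, but it does not threaten the trial's size or the error rate of its primary test. Fifteen per group gives 84% power at two-sided 0.01, not 90%; the exact figures are 18 at 0.01 and 12 at 0.05. The planned 40 per group is ample for the pilot difference at either alpha. That rests on the pilot means and SDs, taken from ten patients per group without randomisation.

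The global hypothesis should not be kept as written. If it includes waiting time, it is likely to be rejected for reasons unrelated to nasal symptoms. The range of about 56% to 100% depends on the assumed 90-minute difference, the assumed SDs of 120 down to 30 minutes, and the assumed set of nine uncorrelated outcomes. It tells the reader nothing about TNSS, and it leaves a chance of up to about 34% of at least one false positive among eight independent null outcomes.

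Severity: should-fix.

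**What to change.** 1. State one two-sided alpha in both the Sample size and Statistical analysis sections: 5%, as the analysis section already has it.
2. Restate the calculated size at that alpha: 12 per group by exact t-test. If 0.01 is kept instead, use it in both places and give 18. Repeat the corrected figure in the Discussion. Enrolment does not change.
3. Delete the global-hypothesis sentence. State that the trial's conclusion rests on a single between-group test of the change in TNSS at week 4.
4. Report the other outcomes as secondary, with estimates and confidence intervals.

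The cost is wording only. The one small downside is that P values for secondary outcomes no longer stand as separate claims.

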## Discussion

Sphenopalatine ganglion stimulation with one acupuncture needle requires knowledge of not only traditional Chinese medicine theory but also neuroanatomy and neurophysiology. Furthermore, it is relatively difficult to study and apply clinically. Considering the proven therapeutic efficiency of verum acupuncture for PER, clinical application of a new technique will be unwarranted if evidence for its advantages cannot be obtained.

The proposed randomized controlled trial will investigate the advantages of sphenopalatine ganglion stimulation with one acupuncture needle over verum acupuncture for treating moderate-severe PER. The trial should show benefits of sphenopalatine ganglion stimulation with an acupuncture needle for treatment of moderate-severe persistent allergic rhinitis, including improvement of the total nasal symptom score, faster onset time, longer duration of effectiveness and shorter treatment time.

Many Chinese acupuncturists and otolaryngologists have discussed the endpoints for our pilot study and concluded that inferior nasal concha swelling and nasal congestion are the most serious challenges in traditional Chinese acupuncture. Further, such treatment does not show clinical effectiveness in a short time. In contrast, sphenopalatine ganglion stimulation with one acupuncture needle can quickly alleviate nasal congestion and inferior nasal concha swelling. Therefore, we have decided to observe the onset time and duration of effectiveness in addition to other outcome measures such as TNSS and TNNSS used in other studies.

Our pilot study revealed that sphenopalatine ganglion stimulation with one acupuncture needle yields significant differences in onset time, duration of effectiveness, TNSS, RQLQ score, and number of post-treatment symptomatic days compared with verum acupuncture. Experts in allergic rhinitis were consulted to decide which endpoints to adopt for sample size calculation. They concluded that changes in TNSS are generally applied, and this scoring system has been validated [18]. Therefore, the mean TNSS was used to calculate the sample size for the trial. Furthermore, the research group consensually decided that TNSS should replace onset time and duration of effectiveness, reported in the ISRCTN registry, as the primary outcome measure of the trial. Only 15 cases per group, total 30, are needed based on the sample calculation. As the small sample size may be increase the risk of bias, we decided to increase the patient number to 40 in each group in consideration of each center’s research capabilities. Allowing a drop-out rate of 20%, 96 participants will be enrolled in the study. All other endpoints are considered as secondary outcome measures. The total IgE level and eosinophil count in venous blood will be measured to investigate the mechanism underlying the effect of acupuncture.

We will measure the clinical waiting time to investigate economic benefits. Sphenopalatine ganglion stimulation with an acupuncture needle requires only approximately 1.5 min and no bed. In contrast, patients spend an average of 2 h to receive acupuncture in Chinese hospitals, including 1.5 h or longer waiting for a bed and 20 min or longer per session.

The proposed trial has several methodological limitations. The acupuncturists and participants cannot be blinded because of the difference in acupuncture techniques and control required while needling. However, the acupuncturists will be trained to not communicate the therapeutic procedures and responses to the participants and outcome assessors. Furthermore, this study will not allow us to determine whether the observed efficacy is caused by placebo effects, intensity of provider contact, or physiological effects of needling. The bias resulting from the lack of blinding cannot be totally excluded. Finally, the sample size is small.

